### Study rationale

#### Rationale for primary aim

CVL-related TE in children is difficult to diagnose. CVL-related TE could be symptomatic (with pain, edema, skin discoloration and dilated veins) or asymptomatic [37,38]. The presence of symptoms reflects the site of obstruction, size of obstruction and acuteness of obstruction. In children, especially in younger age group, the symptoms of TE are difficult to detect. Hence even a significant TE may go un-noticed. Journeycake et al., showed that only 5 of 21 children with CVL-related TE were symptomatic; 10 of 16 “asymptomatic” children had multiple CVL placements prior to the diagnoses of TE [17]. This observation highlights the importance of a reliable screening method for diagnosis of CVL-related TE.

Although compression ultrasonography (USG) is the diagnostic test of choice for suspected lower venous system deep venous thrombosis (DVT), it has poor sensitivity for the diagnosis of DVT in the upper venous system (central subclavian vein, brachiocephalic and superior vena cava) [37,38]. Within the thoracic cage, the non-compressibility of the vessel cannot be assessed due to the bony ribs [39]. Prospective studies have shown that bilateral venography is the most sensitive technique for diagnosis of upper venous system TE within the thoracic cage [37-40]. However, venography is an invasive, cumbersome and painful procedure, and it exposes children to excessive radiation. Hence venography cannot be used as a routine screening tool for evaluation of CVL-related TE in children with cancer. Magnetic resonance venography (MRV) is another non-invasive, safe and reliable method to diagnose DVT. Although safe, MRV is very costly, requires sedation or general anesthesia for younger patients making it unsuitable for screening purposes, and its sensitivity and specificity in children have not been well defined [40]. Further, CVL-related small clots such as fibrin sheath or ball valve thrombi (which are mostly responsible for CVL-dysfunction) may not be detected by USG or even linogram.

Thus, there is no reliable, safe, inexpensive and noninvasive screening tool for diagnosis of CVL-related TE in children. Hence one may have to consider surrogate markers as predictors of underlying TE. An ideal predictor will reliably identify patients with high a probability of underlying TE for whom evaluation by invasive tests will be justified. Considering available evidence, we propose that CVL-dysfunction may be a good predictor of underlying TE. If indeed the presence of CVL-dysfunction can predict TE then such patients could be evaluated further with the gold standard test of venography and treated with anticoagulation therapy. This in turn will reduce the risk of development of symptomatic TE and infection. However, the first step is to confirm the presence (and the strength) of association of CVL-dysfunction and TE in a large prospective study.

#### Rationale for secondary aim 1

Bacterial and fungal infections and sepsis are well-known complications in children undergoing intensive chemotherapy. Presence of CVL increases the risk of infections [17-19,41-43]. Two recent prospective studies conducted in children with cancer and hematological disorders reported infection rates of 0.87 and 1.7/1000 catheter-days [18,19]. In one study, 40% of patients had CVL-related infections and 44% of the episodes required CVL removal [43].

Although the association of CVL with infections has been well documented, only recently investigators have begun to explore the correlation of CVL-related infection with underlying local TE [42,43]. Prospective studies conducted in adult patients have shown that the local or systemic CVL-related infections are likely to increase the risk of TE in patients on therapy for cancer [42,43]. A retrospective study showed increased risk of thrombosis in children with cancer and documented infection [odds ratio (OR) 2.2, p = 0.016] [17]. So far there is no prospective study to evaluate the relationship of TE and infection in children with cancer.

#### Rationale for secondary aim 2

Deitcher et al., reported CVL-dysfunction in 28% children with brain tumors; children with CVL-dysfunction, but not with major TE, had a reduced overall survival [32]. Further, our results suggest that CVL-dysfunction is an independent risk factor for poor OS and EFS in children with cancer [33]. The poor outcome in children with cancer and CVL-dysfunction could be related to the interruption in therapy due to the loss of CVL or due to the associated complications like TE and infection. In addition, CVL-dysfunction may represent activation of coagulation system; a marker of poor prognosis in adults with cancer [32,33,36]. Thus, CVL-dysfunction probably reflects significant underlying pathology. Despite these observations there are so far no prospective studies to evaluate the clinical significance of CVL-dysfunction. Secondary aim 2 evaluates the relationship of CVL-dysfunction with OS and EFS. CVL-dysfunction may herald underlying undetected TE; the early diagnosis of which may prevent complications like overt TE, infection and therapy-delays. This in turn will improve the overall outcome in children with cancer.

#### Rationale for secondary aim 3

Although the three common complications of CVL namely CVL-dysfunction, infection and TE seem to be closely associated, the exact relationship is unclear. One retrospective study in children with cancer showed an increased risk of TE in association with CVL-dysfunction (OR 3.7, p = 0.001) and infection (OR 2.2, p = 0.016) whereas children having both dysfunction and infection had much higher risk of TE (OR 6.4, p<0.001) [17].

Presence of a local clot may lead to CVL-dysfunction as well as may act as a nidus of infection providing fertile ground for growth of the microorganisms. This may lead to either local, CVL-related infection or infection elsewhere in the body. CVL-dysfunction also needs frequent manipulations such as repeated attempts to infuse or withdraw blood; this may increase the chances of infection in immunocompromised patients. On the other hand, presence of infection can potentially initiate activation of coagulation and formation of TE in the vessel which is already damaged by CVL or by hyperosmolar infusions. The small clot developed in the process may progress to cause a significant TE either locally or distally elsewhere in the body. This clot may also lead to CVL-dysfunction.

In summary, the cause and effect relationship of infection as well as the chronological relationship of infection, TE and CVL-dysfunction are still unclear. Figure 1 outlines our proposed hypothesis of the mechanism of interaction of these three CVL-related complications.

**Figure 1 F1:**
[figure not shown]
Possible association of infection, CVL dysfunction and thrombosis.

#### Rationale for secondary aim 4

Currently there are no uniform, standard guidelines for CVL insertion and care in children with cancer [44]. A survey conducted by United Kingdom Children’s Cancer Study Group showed that although 70%-80% of health care professionals thought that the CVL-dysfunction and TE were clinically important problems, there was remarkable variation in the diagnosis, management and prevention of CVL-dysfunction and TE [45]. There are no guidelines for ideal flush solution, its concentration or delivery schedule [23,44,45]. The CVL can be inserted either by an interventional radiologist with percutaneous technique or by the surgeons using cut-down technique. Although for an occasional patient the practice may vary, usually each institution has a consistent protocol for CVL-insertion. We conducted a survey of all five participating institutions evaluating the practice of CVL insertion and the CVL-care guideline. This survey showed that all the participating institutions use different guidelines for the care of the long term CVLs. In three of the five institutions usually surgeons insert the CVLs and in two institutions the interventional radiologists place the CVLs. By evaluating the impact of CVL- and patient-related factors on development of TE, infection and CVL-dysfunction as well as comparing the institutional practice of CVL insertion and care, we hope to develop evidence-based guidelines for CVL-care.

## Methods and design

This is a prospective analytical cohort study conducted at five tertiary care pediatric oncology centers in Ontario. Figure 2 outlines the research design of the study.

**Figure 2 F2:**
[figure not shown]
Flow diagram of the proposed study outlining the patient identification, study enrollment and follow up.

### Justification for study design

Majority of children diagnosed with non-CNS cancer have CVL placed for therapy. Since both TE and infection are complications of cancer-therapy, we have chosen the best study design in observational methodology which is the prospective cohort study.

### Patient population

Children with non-CNS cancer diagnosed and treated at five participating institutions.

### Patient eligibility

#### Inclusion criteria

All children (≤ 18 years of age) newly diagnosed with non-CNS cancer will be eligible for the proposed study. Not all patients with CNS cancers receive CVL and the prevalence of TE in children with brain tumors is very low (< 2%) [32,36,46]. Hence we will include only children with non-CNS cancers.

#### Exclusion criteria

1. Patients with relapsed cancer since they would have had previous exposure to CVL

2. Age > 18 years at cancer diagnosis since majority are treated at the adult facilities

3. Absence of CVL

4. Diagnosis of CVL-dysfunction prior to study enrollment

5. Patients on anticoagulation therapy or prophylaxis

6. Unable or unwilling to provide written informed consent (and/or assent) for the proposed study

### Observations

#### Dependent variables

1. Development of symptomatic TE in any location while receiving therapy for cancer. Screening for asymptomatic TE will not be performed.

2. Clinical or microbiologically proven infection as defined below

3. Recurrence of cancer, second malignant neoplasm (SMN) or death due to any cause

#### Independent variables

1. CVL-dysfunction as defined below

2. Age of the patient at the time of diagnosis of cancer

3. Type of cancer

4. CVL insertion technique

#### Definitions

1. CVL-dysfunction: Persistent or recurrent difficulty in blood draw and/or infusion of at least one CVL lumen with or without the need for instillation of tissue plasminogen activator (tPA) documented on two or more occasions. For a multi-lumen CVL, difficulty in infusion or withdrawal of the same lumen for ≥ 2 occasions is required to fulfill the criteria of dysfunction.

2. Symptomatic thromboembolism: total or partial occlusion of one or more vessels objectively confirmed by at least one radiological diagnostic method prompted by typical clinical symptoms. CVL-related DVT: total or partial occlusion of vessel in which CVL is placed and/or right atrial TE.

3. Infection: Published guidelines will be used for diagnosis of CVL infection [47,48]. In addition a patient will be diagnosed with *infection* in any of the following situations:

For the purpose of this study patients with suspected or proven viral (e.g. influenza, chicken-pox) as well as mycoplasma infection will not be categorized as “infected”.

a. Septic shock requiring Pediatric Intensive Care Unit (PICU) admission with or without microbiological proof.

b. Positive blood culture collected from CVL and/or peripheral vein requiring intravenous (IV) antibacterial and/or antifungal therapy beyond 48 hours.

c. Invasive fungal (including candidial) infection defined as positive blood culture or positive culture from any other site (except oral or perianal candidiasis), radiological documented probable infection requiring systemic antifungal therapy and/or histopathological evidence of fungal infection (e.g. documentation of fungal hyphae on biopsy)

d. Clinically documented infection (e.g. CVL site infection, tunnel track infection, cellulitis, abscess formation at any site, typhlitis), with or without microbiological proof, requiring antibacterial or antifungal therapy beyond 48 hours. Minor infections like suspected otitis media, streptococcal throat infection will be excluded.

e. Persistent and/or recurrent fever of unknown origin requiring antibiotics therapy beyond 7 days.

4. Event: recurrence of cancer, SMN or death due to any cause.

#### Recruitment and consent process

Newly diagnosed cancer patients will be identified through pediatric oncology services at the participating institutions. Study staff will review patients’ records to determine eligibility for the proposed study. Eligible patients will be approached, prior to CVL placement or within two weeks of CVL placement, for informed consent. Reasons for non-participation will be recorded for all screened patients.

#### Study follow-up and study duration

This study will require no visits above and beyond those required for the clinical care of the patient. After initial hospitalization for evaluation and therapy for cancer, all patients are seen frequently (either weekly or monthly) at the outpatient clinics as part of their routine clinical care. Patients will be monitored for infection, disease progression or recurrence, or SMN. After completion of therapy patients are followed life-long according to the “After-Care-Guidelines” recommended by POGO.

Patient enrollment will occur until the required sample size is achieved. We anticipate that the required patient population will be enrolled during first two and half years of the study. Patients will be followed for the development of symptomatic TE until the completion of cancer therapy and final removal of CVL which occurs within 6–12 weeks post completion of therapy. Thereafter overall outcome data regarding continued remission, recurrence of cancer, SMN or death will be collected for each patient every six months for a total period of five years from the initial diagnosis.

#### Ethical considerations

##### Patient safety and inconvenience

This study will not pose any additional risks to the patients. Only pertinent data will be collected prospectively. No additional tests will be performed and there will not be any change in current institutional practice of CVL insertion, care or management of complications.

##### Ethics

This study is conducted in accordance with the Ethical Conduct for Research Involving Humans outlined in Tri-Council Policy Statement [49]. The study has been approved by the Research and Ethics Board (REB) of McMaster University and Hamilton Health Sciences as well as by the REB of each of the participating institution. Participation is fully voluntary after informed consent either from the patient or the parent/guardian as per the REB guidelines. In addition, assent will be obtained from patients 7–15 years of age (or younger if perceived competent to do so by physicians) as per institutional guidelines. Participants are informed about the nature of the study, their rights and obligations and are assured that refusal to participate does not affect patient care.

##### Confidentiality

Procedures are developed to protect the confidentiality of the data collected in accordance with the REB’s requirements and Canadian privacy legislation. All the data will be coded and stored securely to protect individual confidentiality.

##### Patient care and benefit

Patients with TE will be treated and counseled according to the recommended standard of care.

#### Data collection and analyses

##### Clinical data

Will be collected and recorded for all patients on standardized data collection form. In summary, data will include baseline patient characteristics, personal and family history of TE or prothrombotic disorder; diagnosis of cancer and cancer-therapy, details of CVL-dysfunction, details of infections and TE, if any, and overall outcome from cancer.

##### Details of CVL insertion

Details of CVL insertion (including the date, body side, type of CVL used, type of procedure, and any difficulty encountered) will be recorded. For patients requiring more than one CVL during the course of initial cancer therapy, details of each additional CVL will be recorded separately. The life span of the CVL will be measured in “catheter-days” calculated from the time of insertion and time of removal of CVL or the time of death or last follow-up if the CVL was still in place.

##### Diagnosis, evaluation and management of patients with symptomatic TE

To ensure uniformity of diagnosis and evaluation, uniform guidelines for the definition of symptomatic TE including clinical and radiological assessment at the time of diagnosis of TE as published elsewhere will be used. In addition, all patients diagnosed with symptomatic TE (either upper or lower limb or elsewhere in the body) are recommended to undergo bilateral upper venous system venography, contrast enhanced MRV or computerized tomography (CT) venogram to detect CVL-related TE. At the time of diagnosis of TE, laboratory evaluation will include CBC, coagulation profile (INR, APTT, D-dimer, fibrinogen) and measurement of prothrombotic defects as per institutional practice. Patients who develop a symptomatic TE will be managed according to the institutional guidelines. Clinical, laboratory and radiological details as well as management and outcome details of TE will be recorded on the data collection form.

##### Diagnosis, evaluation and management of patients with infection

Clinical and laboratory details of patients fulfilling the definition of “infection” for this protocol will be recorded. Patients with suspected or proven infection will be managed according to the institutional guidelines for the management of infection in an immunocompromised host.

##### Measurement of the exposure (i.e. CVL-dysfunction)

To avoid recall bias in recording CVL-dysfunction, CVL-access information will be collected and recorded prospectively. Currently on the the inpatient unit, every time the CVL is accessed, the nurse accessing the CVL completes the CVL checklist and records any problems in blood-draw, infusion or need for tPA. Similar checklist will be filled out for patients’ outpatient visits as well as emergency room visits, if any. These checklists will be collected and reviewed by the study staff at regular intervals In addition, during the regular clinic visit patients (or care givers) will be asked about the functioning of CVL and any problems encountered and their responses documented. We believe that combination of prospective documentation by nursing staff and patient recall will capture all the events of CVL-dysfunction. The patient will be categorized as “exposed” once the patient has met the criteria for CVL-dysfunction.

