### Strengths and potential limitations of the study

The major strength of the study is the use of a prospective cohort design. Previous studies were single institution studies using retrospective design [17,32,33,36]. These studies report up to 30% of missing data [17,32,33,36]. To avoid this problem we will use uniform data collection forms for all study participants and for patients with TE which is likely to capture all the relevant information. Further, the CVL access data will be collected prospectively and hence the exposure criteria will be recorded properly avoiding any recall bias.

Unlike previous studies, evaluation of CVL-dysfunction is the primary aim of our study which formed the basis of our sample size calculation. By inclusion of only symptomatic and objectively confirmed TE, we will avoid ambiguity over diagnosis, and thus, reporting of TE. Uniform guidelines for diagnosis and evaluation will likely minimize chances of misdiagnosis of TE.

In addition the following steps are taken to minimize sources of errors and likely biases improving internal validity of the study. To avoid selection bias all consecutive newly diagnosed non-CNS cancer patients meeting the inclusion criteria will be eligible and approached for participation in the proposed study. All reported events of TE will be confirmed by an independent adjudication committee. To avoid recall bias CVL access data will be collected prospectively and hence the exposure criteria will be recorded properly. Assessors (radiologists) evaluating for TE will be blinded as regards the “exposure” status to avoid measurement bias. With the use of uniform data collection forms for all study participants and patients with TE, infection and CVL dysfunction, all the relevant information is likely to be captured. Further, all data will be analyzed centrally.

Another strength of the study is that this study is conducted across five pediatric oncology institutions with inclusion of wide range of cancer diagnoses. Hence we think that the findings of the study will be generalizable to pediatric oncology population. The results of this study will also be applicable for adults with cancer as well as to the population of patients with other chronic diseases who need long term CVL.

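### Patient and caregiver recall can count towards CVL-dysfunction, with no stated cut-off at TE, although the protocol says recall bias is avoided

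*Protocol article*

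**What the plan says.** The section on measurement of the exposure opens with its safeguard: "To avoid recall bias in recording CVL-dysfunction, CVL-access information will be collected and recorded prospectively". Nurses complete a checklist whenever the line is accessed on the ward, and similar checklists cover outpatient and emergency visits. The section then adds a second source: "during the regular clinic visit patients (or care givers) will be asked about the functioning of CVL and any problems encountered and their responses documented". It expects the two together to be complete: "We believe that combination of prospective documentation by nursing staff and patient recall will capture all the events of CVL-dysfunction". On classification it says: "The patient will be categorized as “exposed” once the patient has met the criteria for CVL-dysfunction".

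The Definitions section describes dysfunction as difficulty drawing blood or infusing, "with or without the need for instillation of tissue plasminogen activator (tPA) documented on two or more occasions". In a multi-lumen line the same lumen must be affected both times. The definition does not say whose documentation counts.

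The Analysis plan codes dysfunction as present or absent among the pre-specified factors of the logistic model for TE. Time to dysfunction is listed as an independent variable but is not among those factors. Under Strengths and potential limitations, the article states: "the CVL access data will be collected prospectively and hence the exposure criteria will be recorded properly avoiding any recall bias".

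**The concern.** A documented answer from a family can, as the text stands, supply one or both of the qualifying occasions. Questions are put at regular clinic visits, follow-up for TE runs to the end of therapy and final line removal, and nothing stated ends exposure ascertainment at a TE or requires dysfunction to come first. A family may recall earlier line trouble more readily once a clot has been diagnosed. An occasion first reported at that point would still make the child exposed in a present/absent model.

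That would be misclassification of the main exposure that depends on the outcome, which can move the primary OR away from 1. The stated safeguards do not cover it. Radiologists are blinded to exposure and TE events are adjudicated, but both measures protect the outcome. The matter is important because this association is the primary hypothesis, and the Discussion would use it to justify trials of prophylactic anticoagulation.

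**Working it through.** **Setting the text side by side.** Recall is a named source of exposure (Measurement of the exposure). The definition accepts any documentation (Definitions). The model ignores the order of exposure and outcome (Analysis plan). Together these leave a route for outcome-prompted recall to decide exposure status, so a claim of avoiding any recall bias does not follow from the stated design.

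**Inputs, from Sample size.** 450 children, 90 exposed and 360 unexposed; TE in 11% overall, 23% of exposed and 9% of unexposed.

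**The plan's own figure.** 450 × 0.11 = 49.5, which reproduces the stated figure of about 50 events. (The two group rates give 20.7 + 32.4 = 53.1 events, or 11.8%. The difference does not affect this point.)

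**Illustration.** Let f be the share of truly unexposed children with TE who are wrongly counted as exposed, with none moved among children without TE. With a exposed TE, b exposed without TE, c unexposed TE and d unexposed without TE:

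observed OR = (a + f·c) × d / [b × c × (1 − f)]

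*No true association, 11% in both groups:* a = 9.9, b = 80.1, c = 39.6, d = 320.4. Because a/c = 1/4, the formula reduces to (1 + 4f)/(1 − f).

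*The plan's rates:* a = 20.7, b = 69.3, c = 32.4, d = 327.6. True OR = (20.7 × 327.6)/(69.3 × 32.4) = 3.02.

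| f (assumed) | Children moved, null case | OR if truly 1 | OR if truly 3.02 |
|---|---|---|---|
| 0 | 0 | 1.00 | 3.02 |
| 5% | 2.0 | 1.20/0.95 = 1.26 | 3.43 |
| 10% | 4.0 | 1.40/0.90 = 1.56 | (23.94 × 327.6)/(69.3 × 29.16) = 3.88 |
| 20% | 7.9 | 1.80/0.80 = 2.25 | (27.18 × 327.6)/(69.3 × 25.92) = 4.96 |

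In the null case, the approximate probability of a significant result in the harmful direction rises from 0.025 to 0.11, 0.28 and 0.70. This takes the stated alpha of 0.05 as two-sided and uses an unadjusted comparison of two proportions.

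**When over-reporting also occurs without TE.** If 5% of unexposed children are moved in both groups, the null OR stays at 1.00 and 3.02 falls to 2.63. If 10% of unexposed TE cases and 5% of unexposed non-cases are moved, the null OR is 1.23. Inflation needs a difference between the groups, and the size of the difference sets the size of the error.

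**The case against.** The case for the plan has weight on several points.

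- The strengths claim is attached to the line-access data, which are collected prospectively. Recall is a supplement. A reader might infer that the exposure rests on retrospective recall; it does not.
- Every family is asked, at weekly or monthly visits, and answers are documented. For a child who later has a TE, answers given beforehand cannot be shaped by it. Only reports first given afterwards are open to outcome-driven recall, and short intervals limit dating errors.
- Two occasions are required, in the same lumen for multi-lumen lines, so one vague memory is not enough on its own.
- TE in any location counts, and the Background puts about half of symptomatic TE in children with acute lymphoblastic leukaemia in the central nervous system. Those families need not search their memory for line trouble.
- A reader might infer that families are questioned after a TE. The article does not say so. It follows only from regular questioning, continued follow-up and the absence of a stated stop. The full protocol may hold a rule.
- The missing cut-off affects nurses' entries too. Since the article says TE prolongs hospital stay, and each inpatient access generates a checklist, a checklist-only definition could itself depend on outcome unless entries after the TE are excluded.

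All of this stands as a limit on size and certainty, and the last point changes the remedy. It does not remove the mismatch: the article itself names recall as an exposure source and also says that any recall bias is avoided.

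**Conclusion.** The point holds in a limited form. As stated, the design admits recall as a source of exposure without restricting its timing, so the claim of freedom from recall bias is too strong and the primary OR may be inflated. The documents do not show that it will be, and they give no figure for differential reporting. The null ORs of 1.26, 1.56 and 2.25 rest on assumed shifts of 5%, 10% and 20% confined to children with TE. Checklists and frequent visits make a small shift more plausible than a large one. With about 50 events, though, reclassifying some four children is enough to take a null OR to 1.56. This is worth correcting in the exposure definition and does not call the cohort design into question.

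**What to change.** - For the primary analysis, count only qualifying occasions recorded with a date before the TE diagnosis, whatever the source. For the infection analysis, use the date of the infection in the same way.
- Base the primary definition on checklist entries made when the line was accessed, and flag the source of every dysfunction record. Use caregiver reports to prompt a search for a contemporaneous record.
- Run a sensitivity analysis that adds caregiver reports documented before the TE.
- Reword Strengths and potential limitations to say that recall bias is reduced.

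The cost is a few lines of text, one source field and a recording date per dysfunction record, with no added visits or tests. The downside is that some dysfunction outside checklist settings will be missed in the primary analysis. That loss may not be fully independent of outcome, and the sensitivity analysis will show how far the result depends on it.
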